**Secondary Outcome measures:**					
Physical Endurance (6MWT)				X	X
Quality of Life (PDQ-39)				X	X
Exit Interviews					X
Safety					X

**SAM**: StepWatch Activity Monitor;
**ESES**: Exercise self-efficacy scale;
**6MWT**: 6-minute walk test;
**PDQ**-
**39**: Parkinson’s Disease Questionnare-39
**Safety**: Falls, hospitalisation, muscle soreness

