These sessions will be delivered in a conference room located next to the Physiotherapy gym in the primary care centre and will include general information to signpost people to services, the role of the healthcare profession in question. Education is provided on medication, symptoms, diet, and aids, but information that could improve exercise self-efficacy and self-management of exercise programs (such as rest, pacing, goal setting etc) is not provided. Following each education session, a hardcopy of the lecture presentation will be provided, and any pamphlets and leaflets recommended by the speaker. The education sessions will be delivered to both groups together, on the day of the usual care group’s exercise classes (the intervention group will have their exercise class on a separate day). All efforts will be made to keep contamination to a minimum as the participants will sit with their own group and will be asked not to discuss the exercise classes with others, and staff will be monitoring conversations in the room. Family-members will also be encouraged to attend the education sessions.

(3) At home, the participants will be expected to independently complete the exercises twice weekly, and this will be discussed at each exercise class with the registered physiotherapist.

**
*Intervention: Parkinson’s Exercise and Education Program with the Behavioural Change Techniques (PEEP + BC).*
** The BC intervention will consist of usual care and four additional techniques to address behavioural regulation, belief about capabilities and peer support.

(1) During the weekly exercise class, the intended functional benefit of the exercises will be explained to everyone. Support will be given to self-select personal exercise intensity and to manage their own exercise and progressions at home. Peer support, competition, reward, and fun will be strongly encouraged and supported by the registered physiotherapist and physiotherapy assistant. By week six, the participants will be invited to lead the class, with the class leader rotating each week, aiming to be independently managing the class by week 12.

(2) An exercise diary to be completed independently at home daily [

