^, we will focus on accelerometery data only as a measure of physical/walking activity.

Falls and ‘near falls’ are the only measures that will be taken from the Activity Log. These events will be discussed in both groups during weekly one-to-one discussions about adverse event with all participants (at the beginning of the exercise class) and recorded.

**
*Gait and balance.*
** Physical performance will be measured objectively before and immediately after the program using the APDM Mobility Lab system™ (
http://www.apdm.com/mobility/). The APDM Lab system uses coordinated, wearable inertial sensors to precisely analyse quality of gait and balance
^
34
^. It is a portable gait and balance laboratory and allows streamlined gait and balance assessment by making it easy to collect, store, analyse, and interpret balance and gait data from a large set of prescribed tasks
^
34
^. It is a validated device to objectively measure walking and balance in PwP
^
34
^. Five Opals™ (accelerometers) will be attached to participants two feet (ankles) and two arms (wrists) and one at the waist using Velcro straps (provided). The participants will be asked to stand, walk a 3-metre distance, turn around, walk back to the chair, and sit down (Timed Up and Go Test (TUG)). A 2-minute free walk (at the participants self-selected pace) will be recorded also to examine stride length and turns specifically.

**
*Exercise self-efficacy.*
** Exercise self-efficacy will be measured using the Exercise Self-Efficacy Scale
^
35
^ (ESES) at baseline, immediately post-intervention. The ESES is a self-report instrument, validated in PwP
^
34
^, containing ten statements about how confident the person is performing physical activity and exercise
^
36
^. Responses are chosen from a four-point scale with 1 = not at all true to 4 = always true (score range 10–40, higher indicating more confidence
^
36
^.)

**
*Secondary outcome measures.*
** We defined two secondary measures:

*Physical endurance*

Physical endurance will be measured with the six-minute walk test
^
35
^ (6MWT) at baseline and post-intervention. Participants walk continuously for six minutes at their self-selected pace. As recommended, an indoor hallway with the 10m distance will be used, and total distance will be recorded.

*Quality of life (QoL)*

QoL will be measured using the Parkinson’s Disease Questionnaire
^
37

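### The only outcome labelled endurance is a six-minute walk at the participant's own pace on a 10 m course, so its distance largely reflects preferred speed and turning

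*Protocol article*

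**What the plan says.** All of the relevant text is in the Outcomes measures section of the protocol article.

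- **Label.** Under the secondary outcomes: "Physical endurance will be measured with the six-minute walk test". Table 1 carries the same label, and no other outcome is described as endurance. It is one of only two secondary outcomes ("We defined two secondary measures"); the other is the PDQ-39.
- **Instruction.** "Participants walk continuously for six minutes at their self-selected pace". The article does not ask participants to go as far as they can, and it gives no rule on rests.
- **Course and score.** "As recommended, an indoor hallway with the 10m distance will be used, and total distance will be recorded".
- **The other timed walk.** Under Gait and balance, which Table 1 lists among the primary outcomes: "A 2-minute free walk (at the participants self-selected pace) will be recorded also to examine stride length and turns specifically". The length of that course is not given.

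The Research objectives include examining the feasibility of the outcome measures (b) and exploring their range and variability across the whole group (e). The Discussion adds that the study will inform the pilot by looking at how responsive the measures are.

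**The concern.** An endurance test should score what a person can sustain. When the person chooses the pace and is not asked to cover ground, the distance mostly records the chosen pace. The gait battery already records a walk under the same pace wording, so effort does not distinguish the two tests. On a short course the score also includes turning, which the protocol treats as a gait target in its own right.

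What is at stake is the choice of measures for the pilot. If the 6MWT distance does not change over 12 weeks, the team could not tell whether endurance stayed the same or the instruction was insensitive to it. If the distance does change, part of the change may be in preferred speed or turning.

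**Working it through.** The plan states no figure on this point, so there is nothing to reproduce. The check compares the two walks and then gives some illustrative arithmetic.

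**1. The two walks side by side**

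| | 6MWT | 2-minute walk |
|---|---|---|
| Role | Secondary, endurance | Part of gait and balance (primary) |
| Duration | 360 s | 120 s |
| Pace | Self-selected | Self-selected |
| Course | 10 m | Not stated |
| Score | Total distance | Stride length and turns, from sensors |

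The pace wording is shared. Duration and scoring differ. The overlap is therefore real but partial.

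**2. What the distance is made of**

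Let v be straight-line speed, L the course length and c the seconds lost per turn. Over 360 s:

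- distance ≈ 360 × L / (L/v + c)
- share of time spent turning ≈ c / (L/v + c)

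Under the stated instruction v is a preference. Endurance enters only if fatigue slows the person during the six minutes.

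**3. Number of turns** (assumed v of 0.8 to 1.4 m/s, ignoring time lost in turning; turns = lengths needed, rounded up, minus 1)

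- v = 0.8: 0.8 × 360 = 288 m; 28 turns on 10 m, 9 on 30 m
- v = 1.0: 360 m; 35 turns on 10 m, 11 on 30 m
- v = 1.4: 504 m; 50 turns on 10 m, 16 on 30 m

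The 30 m course is a comparison only. It is not a standard taken from the documents.

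**4. Share of time turning** (assumed v of 0.8 to 1.2 m/s, c of 1 to 3 s)

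- 10 m: from 1/(12.5 + 1) = 7.4% to 3/(8.33 + 3) = 26.5%
- 30 m: from 1/(37.5 + 1) = 2.6% to 3/(25 + 3) = 10.7%

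**5. Distance can move with endurance held fixed** (10 m course, no fatigue term)

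- Preferred speed 1.0 to 1.2 m/s at c = 2 s: 3600/12 = 300 m becomes 3600/10.33 = 348 m, a gain of 48 m.
- Turn cost 2 s to 1 s at v = 1.0 m/s: 300 m becomes 3600/11 = 327 m, a gain of 27 m. On 30 m the same change is 10800/32 = 337.5 m to 10800/31 = 348.4 m, about 11 m.

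The speeds and turn costs are assumptions. The arithmetic shows the mechanism and does not estimate what this trial will see.

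**The case against.** The strongest reply is that six minutes of sustained walking has an endurance element at any pace, and that the pace wording may be shorthand for a self-paced test. The protocol also describes its course as recommended and cites a source for the test, which cannot be checked here. This stands against any claim that the test departs from a standard, and no such claim is made. It does not rescue the wording: if a maximal-distance instruction is intended, the article says something else.

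A reader might infer more than the text supports:

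- **That the 6MWT repeats the 2-minute walk.** It lasts three times as long and is scored on distance, whereas the shorter walk is scored on stride length and turns.
- **That it adds turning relative to that walk.** The 2-minute course length is not stated. If both walks used 10 m, turns per minute would be about equal.
- **That it does not measure endurance at all.** Fatigue over six minutes can still lower the distance.
- **That participants who pause are lost.** Nothing says so, and a total distance exists with or without a rest. Completed assessments and missing items are tracked under the feasibility outcomes in Table 2.
- **That coaching biases the comparison between arms.** The intervention text, "Support will be given to self-select personal exercise intensity", concerns exercise and its progression, not pace in an assessment. The analysis is descriptive, and objective (e) looks across the whole group.

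Turning is also a constant feature of a fixed course unless turning itself changes. That limits its effect on change scores but does not remove it in a programme that trains dynamic balance.

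**Conclusion.** The concern holds as a mismatch between label and instruction. The only outcome called endurance is walked at a preferred pace on a 10 m course, and its distance will largely reflect preferred speed and turning. It is a weak measure of endurance with partial overlap with the gait battery. A null change could not be read as unchanged endurance.

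The conclusion rests on the article's wording being the instruction actually given. Its size cannot be fixed from the documents; the turn counts, time shares and metre differences above depend on assumed speeds and turn costs. The consequence is modest, because this is a secondary outcome in 20 people with descriptive analysis. It still merits correction, because assessing the outcome measures is one of the study's stated purposes.

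**What to change.** Settle one of two options before the first baseline assessment:

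1. **Keep the endurance label and change the instruction.** Ask participants to cover as much distance as possible in six minutes. Allow rests, record them, and let the clock run. Use one written script at both visits. Keep the same 10 m course at both visits, as the protocol already implies.
2. **Keep the comfortable-pace instruction and change the label.** Report comfortable-pace walking distance on a 10 m course, and stop calling it physical endurance in the text and in Table 1.

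If baseline tests have already been done under the present wording, take the second option, because changing the script between visits would break the pre-post comparison.

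The cost is a line or two in the protocol and the assessor script, with no extra visit, staff or equipment. The first option makes the test slightly more effortful. A longer hallway or a count of turns would be optional extras.

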### Data collection

Baseline data will include personal information such as demographics (including age and self-reported sex), social history, medical history, disease severity (using the United Parkinson’s Disease Rating Scale – motor exam) and medication history will be collected before randomisation by the research physiotherapist (LA) and the Stepwatch Activity Monitor will be programmed and, as per the manufacturer’s instructions, attached to the participants ankle at the end of the assessment. They will be instructed to wear the accelerometer continuously for seven days, until they return the following week, when the device is removed the data will be downloaded onto a password protected file on the research laptop. Participants will be encouraged to contact the research physiotherapist with any concerns about the accelerometer during the week, and a courtesy call will be made during the week to ensure data collection.

Similarly, the participants will be asked to wear the accelerometer for the final week of the program. On the last day of the program, the accelerometer will be removed, and the data will be downloaded. The outcome assessments will be completed by a blinded registered physiotherapist, who is fully trained in the completion of the assessments.

**
*Adherence.*
** Full adherence to the intervention will be defined as follows: 1) attending the baseline and immediate post-intervention assessments, 2) completing 12 weekly activity diaries and 3) attending all 12 exercises classes, attending all 12 education sessions. Attendance at the exercise classes and education sessions will be documented each week by the registered physiotherapist. Activity diaries will be viewed each week during the weekly one to one weekly conversations between the registered physiotherapist and the participant before each exercise class.

**
*Qualitative process evaluation.*
** All participants will be asked to complete a feedback survey [
*Extended Data: Appendix C*] with open-ended questions exploring what they liked/disliked about the PEEP program, elements of the program they felt were not required, or elements they believe should have been included in the program, and their opinions of the topics covered during the education sessions. On-line semi-structured interviews exploring the acceptability of the behavioural change techniques will be conducted a research physiotherapist ([name]) with the intervention participants only, immediately post-intervention (12 weeks). Participants will be asked to discuss the perceived impact and value, and how the intervention address barriers to exercise and physical activity. The interview guide will be informed by previous research examining the acceptability of BC interventions
^
38–
40
^ coded under the domains of the Theoretical Domains Framework
^
20
^. [
*Extended Data: Appendix D*]

### Data analysis

**
*Quantitative analysis.*
** With small numbers in each group, we will present and treat all continuous data as non-parametric data. Suitable summary statistics (e.g., median, interquartile range, and frequency, percentages) will be provided for all outcomes.

These summary statistics will be used to assess the feasibility of the intervention. Potential ambiguities regarding standard safety procedures, types and numbers of measures undertaken to assure patient safety, and types and numbers of unforeseen safety issues will be reported and disaggregated by sex. We will analyse the results according to a modified intention-to-treat principle, whereby we will exclude only patients with no follow-up measurements at all.

**
*Qualitative analysis.*
** Data from the semi-structured interview questions will be audio- recorded, transcribed verbatim, and analysed with the data from the surveys using qualitative content analysis. Difference between the sexes will be carefully considered.

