**Methods:**

A parallel-arm single blinded randomised feasibility study. Twenty participants with Parkinson’s (Hoehn and Yahr stage 1-3) will be recruited from a physiotherapy primary-care waiting list. Following written consent, and baseline assessment, the participants will be randomly allocated to the intervention (n=10) or the control group (n=10). Both groups will receive usual care, which includes a weekly program of a multidisciplinary education, a supervised exercise class and a prescribed home exercise program. The intervention group will receive additional behavioural change techniques, targeting behaviour regulation, belief about capabilities and social influences. Class and home exercise adherence, behavioural component uptake and adherence, and negative events will be recorded. Outcomes will include enrolment and maintenance rates, physical function, falls, physical activity, and exercise self-efficacy measured pre- and post- the 12-week program (in-person). Surveys will be used to compare experiences and satisfaction between groups. Exit interviews will be completed with the intervention group only, exploring their experience of the behavioural change techniques.

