### Participants and recruitment

Participants will be recruited from the current waiting list to attend the existing PEEP Program. We plan to recruit 20 participants (10 in each arm) – to optimise numbers while keeping safety paramount in the classes (n=5 per class). We will aim to recruit an equal representation of both sexes (based on self-report). We estimate an attrition rate of 20%, based on previous PEEP programs and available literature
^
26,
27
^. Prior to random concealed allocation, a member of the research team (LA) will screen participants for eligibility, as follows:

Diagnosis of idiopathic Parkinson’s Disease, confirmed by neurologist or geriatrician.Early Stages of Parkinson’s, as determined by Hoehn & Yahr Stage 1–3 using the United Parkinson’s Disease Rating Scale).Ability to drive or obtain transport that will drop and collect at the health centre.Ability to independently walk (with or without a walking aid).Reported by the referring healthcare provider or carer as able to follow instructions and carry out the exercise program independently at home.

Participants will be excluded if they have:

A diagnosis of atypical Parkinson’s (e.g., progressive supranuclear palsy, multiple system atrophy, etc) or vascular Parkinsonism or drug-induced parkinsonismPreviously completed the PEEP program.Had a hospital admission < 6 weeks ago.Immobility, or are a wheelchair-user.Severe visual or auditory impairmentSerious medical conditions in major organs (heart, lung, or kidney) or other illnesses which prevent independent ambulation or safe exercise.Been identified as a high falls risk (identified during the pre-screening using objective measure the Short Physical Performance Battery (a score of ≤6 indicates a higher fall risk in old adults
^
28
^) and subjective reporting of two or more falls in the past year.

All participants must provide GP clearance letters deeming them medically safe to partake in the exercise component prior to enrolling in the study. Written consent will be obtained from the participants (by LA) before data collection. Participants will be informed that they may withdraw from the study at any time for any reason.

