### Randomisation

Following written consent and baseline assessment (to ensure blinded assessment), a research staff member ([name]), not involved in the screening or data collection, will randomly assign eligible participants in a 1:1 ratio, stratified by sex, using a computer-generated randomisation sequence and concealed allocation (sealed envelopes), to the PEEP or the PEEP + BC group. Outcome assessors will be blinded to group allocation. Study participants will be instructed not to share any information on group allocation with the assessor or with other PwP outside the intervention. Every attempt will be made to ensure the assessor is not unblinded; if this occurs, a substitute assessor will be used. The assessor will not be in the facility while the program is being delivered. A full CONSORT
^
25
^ flow diagram is presented in
Figure 1 and will be populated throughout the study. The participant timeline is documented in
Table 1.

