### Outcomes measures

**
*Feasibility outcomes.*
** Feasibility outcomes of interest include methodological, procedural and clinical uncertainites
^
25,
29,
30
^, examination of recruitment rates, consequences of eligibility criteria, attrition once recruited, data collection completion, resources needed to complete the intervention and the data collection, participant adherence to the intervention, and acceptability of the intervention and study procedures to participants. Feasibility outcomes are shown in
Table 2
^
31
^.

**Table 2. T2:** Overview of feasibility outcomes
^
31
^.

Outcome	Evaluation
Recruitment and eligibility	- Number of patients on current waitlist - Percentage assessed for eligibility; fulfilling inclusion criteria, and included (of total number identified) - Ambiguities regarding eligibility criteria - Reasons for ineligibility - Reasons for non-participation
Data Collection	- Percentage of completed assessments. - Ease of completion and number of missing items - Types and number of potential clinical uncertainties in interviews
Attrition	- Rate of study dropout - Rate of intervention dropout
Resources needed to complete the study and intervention	- Length of time required for: - Participants to work through intervention. - Participants to complete questionnaires and interviews - Study personnel to administer the study
Adherence to the intervention	Number of: - Completed activity diaries. - Exercise classes attended. - Education sessions attended.
Acceptability and experience of the intervention and data collection and exploration of mechanisms of impact	- Reasons for poor attendance and withdrawal from the study and intervention - experience and perception of the behavioural change intervention (including positive and negative consequences) - perceived value of completing home exercise diaries - perceived value of WhatsApp group - perceived value of one-to-one conversations at each exercise class - perceived confidence in self- management - Number and severity of negative events

**
*Process outcomes.*
** The following will be collected to indicate the study process feasibility:

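### The modified ITT rule is stated for all results, so as written it also takes participants without week-12 data out of the adherence, completion and safety summaries

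*Protocol article*

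**What the plan says.** The Quantitative analysis paragraphs of the protocol article first promise descriptive summaries for every outcome, and then say "These summary statistics will be used to assess the feasibility of the intervention". They go on to safety reporting, split by sex, and close with the analysis set: "We will analyse the results according to a modified intention-to-treat principle, whereby we will exclude only patients with no follow-up measurements at all". Nothing in these paragraphs limits that last sentence to a class of outcome, and nothing says what counts as a follow-up measurement.

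Other sections bear on how the rule works:

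- Abstract, Methods: the outcomes are "measured pre- and post- the 12-week program (in-person"). Table 1 likewise has a single post-baseline column after T0, at week 12, and places safety in that column only.
- Participants and recruitment: "We plan to recruit 20 participants (10 in each arm"), and "We estimate an attrition rate of 20%, based on previous PEEP programs and available literature".
- Outcomes measures, Table 2: the feasibility outcomes include "Rate of study dropout - Rate of intervention dropout", the percentage of assessments completed, diaries completed, classes and education sessions attended, reasons for withdrawal, and negative events.
- Safety and Adherence: adverse events, attendance and diaries are recorded or reviewed week by week. Full adherence requires, among other things, attending the post-intervention assessment.
- Randomisation: a CONSORT flow diagram will be filled in as the study proceeds.

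**The concern.** A feasibility study needs two kinds of denominator. Change from baseline in step count, gait or questionnaire score can be described only for people who have a post-programme value. Attendance, diary completion, full adherence, completeness of assessment and adverse events should be described for everyone randomised, because stopping early is part of what is being measured. The article gives one rule for both kinds.

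With a single follow-up visit, excluding people who have no follow-up measurement means conditioning on having reached week 12 in some form. For full adherence this selects participants on a component of the outcome itself. For attendance, diaries and adverse events it discards weekly records that exist for people who later leave.

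At stake are figures that the abstract says will inform the future pilot trial (acceptability, maintenance, protocol integrity). If they are computed on the reduced set, they describe those who stayed while appearing to describe those who were randomised. The modified intention-to-treat label makes this harder for a reader to notice.

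**Working it through.** **Inputs.** N = 20, 10 per arm, and attrition d = 20% (both from Participants and recruitment). One follow-up assessment, at week 12 (Abstract, Methods; Table 1). The sample size is set by class capacity and safety, so there is no power calculation to reproduce.

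**Step 1: expected size of the set.** Expected leavers = 20 × 0.20 = 4, and 20 − 4 = 16 remain (8 per arm if losses are balanced). If dropouts are independent, the chance of at least one is 1 − 0.8^20 = 98.8%, so the choice of denominator will almost certainly matter.

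**Step 2: assessment completion at week 12.** Assume all four leavers have no week-12 data.

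- All randomised: 16/20 = 80%, exact (Clopper-Pearson) 95% CI 56.3% to 94.3%.
- Set left by the rule: 16/16 = 100%, exact 95% CI 79.4% to 100%.

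The second figure is 100% by construction. If baseline assessments are counted too, the contrast is (20 + 16)/40 = 90% against 32/32 = 100%.

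**Step 3: general size of the inflation.** If the excluded people add nothing to the numerator, the percentage is multiplied by 1/(1 − d) = 1/0.80 = 1.25. This applies to full adherence, because someone who misses the post-intervention assessment cannot meet the definition. With illustrative (assumed) counts of fully adherent participants:

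| Fully adherent | Of 20 randomised | Of 16 kept |
|---|---|---|
| 8 | 40% | 50% |
| 12 | 60% | 75% |
| 16 | 80% | 100% |

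If full adherence is computed in the intervention arm alone and two of ten are lost, the factor is again 10/8 = 1.25. For attendance and diaries, leavers contribute something before they stop. If their mean is a fraction r of the stayers' mean, the factor is 1/(0.80 + 0.20r), which lies between 1.25 (r = 0) and 1 (r = 1). So 1.25 is an upper limit for these outcomes.

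**Step 4: sensitivity.**

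- If only some of the four leavers lack week-12 data, the Step 3 limit becomes 20/19 = 1.05 (one), 20/18 = 1.11 (two) or 20/17 = 1.18 (three).
- If attrition were 10% or 30% (assumed range), it would be 1/0.90 = 1.11 or 1/0.70 = 1.43.

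**Step 5: attrition and safety.** On all randomised, attrition is 4/20 = 20% (exact 95% CI 5.7% to 43.7%). On the reduced set it would be 0/16 = 0% (0% to 20.6%), which makes no sense as an outcome. For safety, the number of events can only fall or stay the same when people are removed. The rate per participant could move either way, and the documents do not allow its direction to be fixed.

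**The case against.** The best counter-argument is that the rule was never meant to reach the feasibility outcomes. Table 2 names study and intervention dropout, assessment completion and reasons for withdrawal. The process outcomes name dropout again, and a CONSORT diagram will be populated. Recruitment has its own denominator in Table 2, namely everyone identified. A dropout rate on a set without dropouts is meaningless, so a sensible reader would confine the rule to the pre/post outcomes. There the analysis is descriptive, with medians and percentages and no stated test, and leaving out people with no post value does little harm. Denominators by outcome are also commonly left to a fuller document.

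Much of this stands. A reader might infer that the rule conceals dropouts; the planned dropout outcomes and flow diagram contradict that. A reader might also infer that everyone who leaves before week 12 is removed. That is not supported either: Table 2 separates intervention dropout from study dropout, and someone who stops classes but attends the assessment stays in. Because follow-up measurement is undefined, some leavers might even be kept on the strength of weekly records. Nor is the set a complete-case set, since one week-12 component, such as a questionnaire, is enough to be retained.

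What does not stand is the appeal to a fuller document. The article is not silent here. It states a rule for the results as a whole, directly after the feasibility and safety sentences, and a dropout count in a flow diagram does not correct the denominators of the adherence, completion and safety summaries.

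**Conclusion.** The point holds as one of scope, definition and labelling. The rule as written covers outcomes for which it is unsuitable. With one follow-up visit it yields an available-case set under an intention-to-treat name, and the term that decides membership is left undefined.

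Followed literally at 20% attrition, it inflates adherence and completion percentages by up to 1.25-fold. This rests on two assumptions: that the protocol's attrition estimate is borne out, and that all four leavers lack week-12 data. The factor is smaller if some return for assessment or, for attendance and diaries, if leavers took part before stopping.

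Two further inferences should be resisted. The article gives no numerical progression threshold and speaks of informing a future pilot, so these percentages cannot be said to decide whether it goes ahead. A bias that differs between arms is possible, given the extra demands on the intervention group, but nothing in the document demonstrates it.

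**What to change.** Replace the single sentence with two statements.

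1. Week-12 performance and questionnaire outcomes are described in an available-case set: randomised participants, in their allocated group, with any week-12 measurement, and with the number contributing shown for each measure. Drop the modified intention-to-treat label, and state that weekly attendance, diary and adverse-event records do not count as follow-up measurements for this purpose.
2. Attrition, attendance, diaries, full adherence, data completeness and safety are summarised on all randomised participants (for diaries, all those randomised to a group that is given one). Sessions after withdrawal count as not attended, and adverse events are counted up to withdrawal. Recruitment keeps the denominator already given in Table 2.

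This needs no extra participants, visits or data, because the weekly records are already collected. The only cost is that reported adherence and completion will look slightly less favourable.
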